# Evaluate the safety and efficacy of dura sealant patch in reducing cerebrospinal fluid leakage following elective cranial surgery (ENCASE II): study protocol for a randomized, two-arm, multicenter trial

**DOI:** 10.1186/s13063-022-06490-8

**Published:** 2022-07-20

**Keywords:** CSF leakage, Dura, Sealing, Prevention

## Abstract

**Background:**

Cerebrospinal fluid (CSF) leakage is a frequent and challenging complication in neurosurgery, especially in the posterior fossa, with a prevalence of 8%. It is associated with substantial morbidity and increased healthcare costs. A novel dural sealant patch (LIQOSEAL) was developed for watertight dural closure. The objective of this study is to clinically assess the safety and effectiveness of LIQOSEAL as a means of reducing intra- as well as postoperative CSF leakage in patients undergoing elective posterior fossa intradural surgery with a dural closure procedure compared to the best currently available dural sealants.

**Methods:**

We will conduct a two-arm, randomized controlled, multicenter study with a 90-day follow-up. A total of 228 patients will be enrolled in 19 sites, of which 114 will receive LIQOSEAL and 114 an FDA-approved PEG sealant. The composite primary endpoint is defined as intraoperative CSF leakage at PEEP 20 cm H_2_O, percutaneous CSF leakage within 90 days of, wound infection within 90 days of or pseudomeningocele of more than 20cc on MRI or requiring intervention. We hypothesize that the primary endpoint will not be reached by more than 10 patients (9%) in the investigational arm, which will demonstrate non-inferiority of LIQOSEAL compared to control.

**Discussion:**

This trial will evaluate whether LIQOSEAL is non-inferior to control as a means of reducing CSF leakage and safety

**Trial registration:**

ClinicalTrials.gov NCT04086550. Registered on 11 September 2019

**Supplementary Information:**

The online version contains supplementary material available at 10.1186/s13063-022-06490-8.

## Administrative information

Note: the numbers in curly brackets in this protocol refer to SPIRIT checklist item numbers. The order of the items has been modified to group similar items (see http://www.equator-network.org/reporting-guidelines/spirit-2013-statement-defining-standard-protocol-items-for-clinical-trials/).

## Introduction

### Background and rationale {6a}

Cerebrospinal fluid (CSF) leakage is a frequent and challenging complication in neurosurgery, with a prevalence of 8% [1]. Risk factors include posterior fossa surgery, the size of the durotomy, and patient-related factors such as immune-status [2]. It is associated with substantial morbidity and increased healthcare costs, estimated at $10,000–15,000 per patient per leakage [3]. CSF-related complications include delayed wound healing, meningitis and surgical site infection which often require prolonged hospital stay, antibiotic treatment, reoperation, or external lumbar drainage. To prevent CSF leakage, various dural sealants were developed to augment watertight closure of the dura. Thus far, their use has not shown a significant effect in reducing the number of complications [1].

The sponsor of this study has developed a dural sealant patch (LIQOSEAL®, Polyganics BV) (Fig. 1). LIQOSEAL is designed to serve as an adjunct to primary dural closure in cranial surgery. Preclinical studies have shown that LIQOSEAL has advantages in dural adherence and burst pressure compared to other sealants [4]. The first in-human study [5] (ENCASE) showed that LIQOSEAL is safe and easy to use. However, a clinical comparative study testing its efficacy compared to control in humans has not been performed yet.

**Fig. 1 Fig1:**
[figure not shown]
LIQOSEAL, investigational device. Length 8 cm, width 8 cm, and weight 1600 to 2000 mg

### Objectives {7}

The objective of the current ENCASE II study is to clinically assess the safety and effectiveness of LIQOSEAL as a means of reducing CSF leakage in patients undergoing elective posterior fossa intradural surgery, by showing non-inferiority compared to a control group.

### Trial design {8}

This study protocol adheres to the SPIRIT reporting guidelines. The SPIRIT checklist is supplemented as supplementary file 1. This study follows a randomized controlled, international, multicenter design with a 90-day follow-up. Patients will be randomized to receive LIQOSEAL or control (DuraSeal® (Integra) or Adherus® (HyperBranch, Medical Technology)) to be applied after the primary closure of the dura with suturing. Patients will be allocated in a 1:1 ratio to interventional device or control. The framework of this trial is noninferiority.

## Methods: participants, interventions, and outcomes

### Study setting {9}

This study will be conducted at up to 20 high volume neurosurgical centers in the USA and Europe. A complete list of participating sites can be found in appendix I.

### Eligibility criteria {10}

Preoperative inclusion criteria for participantsPatients who are able to provide written informed consent prior to participating in the clinical investigation.Age ≥ 22 years.Patients who are able to comply with study requirements.Patients scheduled for elective surgery including a trepanation to reach the subdural infratentorial space (with lower limit of incision defined as the lower edge of C2) with closure of the dura.Female patients of child bearing potential must agree to use contraception from the time of signing the informed consent form (ICF) until 90 days post-surgery.

Preoperative exclusion criteria for participantsFemale patients who are pregnant or breastfeeding.Assumed impaired coagulation due to medication or otherwise.Presence of infection.Any type of dural diseases in planned dural closure area.Patients requiring re-opening of planned surgical area within 90 days after surgery.Known allergy to any of the components of LIQOSEAL, DuraSeal, or Adherus.Patients who previously received a LIQOSEAL, DuraSeal, or Adherus.Patients who previously participated in this study or any investigational drug or device study within 30 days of screening.Presence of hydrocephalus (which will not be resolved by the surgical procedure).Patients with contra-indication to MRI.

Intraoperative inclusion criteria for participantsSurgical wound classification Class I/Clean.Minimally 5 mm of dural space surrounding dural opening.

Intraoperative exclusion criteria for participantsPatients in whom elevation of PEEP has a potential detrimental effect.Patients who will require a CSF drain, electrodes, or other devices passing the dural layer or extra- to intracranial bypass surgery.Primary closure of the dura mater with material other than autologous material excluding fat.Patients in whom no intraoperative CSF leakage is present after primary closure of the dura mater with elevation of PEEP.A gap of > 3 mm after primary closure of the dura mater.Dural opening cannot be covered by LIQOSEAL (8×8 cm) with a 5-mm overlap.

Eligibility criteria for surgeons performing the intervention

Only neurosurgeons and neurosurgical residents trained for the protocol and application of both the interventional and control device will perform the study interventions. Virtual training will be provided by the sponsor during the site initiation visit and online revision material is available throughout the study. Only trained and signed off surgeons can perform study actions. A delegate from the sponsor also attends the first surgery if wished for by the local center.

### Who will take informed consent? {26a}

Informed consent will be collected by the principal investigator or designated study team member.

### Additional consent provisions for collection and use of participant data and biological specimens {26b}

Participants will be asked to consent or not to the use of their data for other research related to the investigational device, to be contacted for future studies and to share video/photographs of the surgery with the sponsor of the study.

### Interventions

#### Explanation for the choice of comparators {6b}

##### Investigational device description

The bioresorbable LIQOSEAL is indicated for use as an adjunct to standard methods of dural closure, such as suturing, to provide a watertight closure of the dura. LIQOSEAL consists of two layers: a watertight blue layer comprising biodegradable polyesterurethane and an adhesive white layer comprising biodegradable poly(DL-lactide-co-ε-caprolactone) copolymer and multiarmed N-hydroxylsuccinimide functionalized polyethylene glycol. This layer reacts with amines in the dural tissue in a moist environment, forming covalent bonds between the device and the tissue.

##### Control device description

The control arm of this study consists of two Food and Drug Administration (FDA) approved dural sealants for cranial use: DuraSeal and Adherus, indicated for use as an adjunct to standard methods of dural repair. Both consist of 2 components that when mixed together form an absorbable hydrogel. These products can be considered the current standard of care for dura sealing [6, 7].

#### Intervention description {11a}

The patient is electronically randomized for LIQOSEAL or control device on the day of surgery by trained personnel other than the operating surgeon.The assigned dural sealant is taken out of the freezer/storage and placed in a non-transparent box.First PEEP test (for safety).Dura mater is closed with the standard method of suturing.Hemostasis should be achieved.The dura mater surface is rinsed from particles with physiological saline and kept moist.Second PEEP test (CSF leakage confirmed).Surgeon is unblinded and the dural sealant is applied.For LIQOSEAL: the dry patch is cut into the required size and positioned with the white side against the sutured area of the dura mater and compressed for 2 min with a moist gauze.For Duraseal and Adherus: the hydrogels are applied aiming at the sutured area of the dura mater, holding the device 2–4 cm away, until a thin coating (1–2 mm) is formed.9.Third PEEP test (2 min after device implantation).10.Standard closure of cranial defect and soft tissue will then be undertaken per surgeon standard.

#### Criteria for discontinuing or modifying allocated interventions {11b}

Once the patient is allocated to the control or interventional arm the patient can still be excluded from the study in case the intraoperative eligibility criteria are not met or in case the first PEEP test was not considered safe for the patient. Once the allocated intervention has been applied, this can be modified in case the patient reaches the primary outcome during the surgery (intraoperative CSF leakage at the third PEEP test). In such case, the neurosurgeon can undertake any actions deemed necessary to ensure optimal patient care in the situation.

#### Strategies to improve adherence to interventions {11c}

There is no patient action required to adhere to the intervention protocol. Surgeons are blinded until after primary closure of the dura to optimize adherence to the interventions independent of the allocated intervention.

#### Relevant concomitant care permitted or prohibited during the trial {11d}

Participants are not allowed to participate in any other investigational drug or device study. All other forms of treatment are permitted.

#### Provisions for post-trial care {30}

Insurance is in place, to enable compensation in the event of an injury to a participant.

#### Outcomes {12}

##### Primary endpoint

The primary endpoint is a composite endpoint defined as the occurrence of any of the following within 90 days of surgery:

Wound infection defined in accordance with the Centers for Disease Control and Prevention guidelines as deep incisional (cat II) or organ or space infection (cat III) [8].Intraoperative CSF leakage after device application at a positive end expiratory pressure (PEEP) of 20 cm H_2_O.Percutaneous CSF leakage confirmed by β-2 transferrin test.Pseudomeningocele requiring puncture, external lumbar drainage or surgical re-intervention.Pseudomeningocele >20 cc as confirmed on MRI.

##### Secondary endpoints

*Safety*
Device-related adverse events (AEs) and serious adverse events (SAEs) throughout the study up to 90 days after surgery.Complications requiring surgical re-intervention up to 90 days after surgery.

*Performance*
Any pseudomeningocele as confirmed on magnetic resonance imaging (MRI) at day 90.Volume of pseudomeningocele as determined on MRI at day 90.Ease of use and application of the LIQOSEAL

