#### Procedure for unblinding if needed {17b}

The surgeon is unblinded after finalization of the primary closure of the dura, to apply the allocated device.

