##### Postoperative data

During the hospitalization, the subject will be monitored daily for clinical signs of infection. The surgical wound will be inspected daily starting 24 h after surgery. Blood analysis and a wound culture will be performed if there are clinical signs of infection. In case of CSF leakage from the incision, a β-2 transferrin test will be performed. Data will be collected every 24 h from 24 h after surgery until discharge or day 7 (whichever comes first).

The clinical data to be collected on the e-CRF includes the following: body temperature.

In case of signs of infection, the following data will be collected as well: C-reactive protein (CRP), leucocytes, and culture of wound.

The signs of infection will be classified to the Centers for Disease Control and Prevention (CDC) standard of Surgical Site Infection (SSI) and recorded in the e-CRF.

All subjects will undergo an MRI on day 90. The MRI will be performed to collect data on the presence and amount of pseudomeningocele (any subcutaneous fluid on T2) as well as the long-term thickness of dura mater and investigational device.

Independent radiologists will analyze the MRIs of all subjects for the outcome measurements. Each MRI will be evaluated by 3 independent radiologists, whereas the analysis then will be based on minimally 2 out of 3 evaluations (whom are in consensus).

Postoperative assessments are not blinded.

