#### Adverse event reporting and harms {22}

During the study, (serious) adverse events and (serious) anticipated and unexpected adverse device effects will be recorded; reporting will be done from point of enrolment till end of study.

The (principal) investigators shall report all adverse events and device deficiencies in the appropriate sections of the e-CRF and provide where requested by the sponsor, the necessary clinical or technical information that may contribute to clarifying the circumstances.

The (principal) investigators shall report all serious adverse events (SAEs) and device deficiencies (DDs) that might have led to a SAE if (a) suitable action had not been taken or (b) intervention had not been made or (c) if circumstances had been less fortunate, and new findings/updates in relation to already reported events to the sponsor and record in the e-CRF within 24 h after awareness of the event.

Any other reportable events as described above or a new finding/update to a reported event shall be reported immediately, but not later than 7 calendar days following the date of awareness by the sponsor of the new reportable event or of new information in relation with an already reported event.

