## Discussion

This is the first randomized controlled trial in which the safety and efficacy of LIQOSEAL will be compared to the best current practice. This trial will evaluate whether LIQOSEAL is non-inferior to control as a means of reducing CSF leakage and safety.

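### One of the two secondary safety endpoints counts adverse events only if judged device-related, in a trial without blinded assessment, and the non-inferiority claim is extended to safety although only the primary composite has a margin and test

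*Protocol article*

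**What the plan says.** The protocol article lists two safety endpoints under Secondary endpoints. The first is "Device-related adverse events (AEs) and serious adverse events (SAEs) throughout the study up to 90 days after surgery". The second is "Complications requiring surgical re-intervention up to 90 days after surgery", which carries no condition on relatedness.

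On blinding, the section on unblinding {17b} states: "The surgeon is unblinded after finalization of the primary closure of the dura, to apply the allocated device". The section on postoperative data adds: "Postoperative assessments are not blinded". The abstract calls the investigational patch novel, and the control device description presents the two comparators as current standard of care.

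On data capture, the section on adverse event reporting {22} says that investigators "shall report all adverse events and device deficiencies in the appropriate sections of the e-CRF". Collection is therefore not restricted to related events.

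On analysis, section {20a} places all safety analyses in the ITT set by randomised assignment, and section {20b} plans no supplementary or sensitivity analyses for safety and secondary endpoints.

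On the claim, the Discussion says: "This trial will evaluate whether LIQOSEAL is non-inferior to control as a means of reducing CSF leakage and safety". The abstract says the same, and Objectives {7} ties both safety and effectiveness to a showing of non-inferiority. The 10% margin in Sample size {14} and the test in {20a} concern the primary composite alone.

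**The concern.** Whether an event was caused by the sealant or by the operation often cannot be settled in a single patient. The Background itself links delayed wound healing, meningitis and surgical site infection to CSF leakage, so such events have causes other than the sealant. Randomisation answers the causal question by comparing all events between arms. A relatedness filter puts individual opinion ahead of that comparison. Where those giving the opinion may know the allocation, and expectations of a new product and of familiar ones may differ, labelling can differ by arm. It can then produce a difference that does not exist or mask one that does. With no sensitivity analysis planned for safety, the article offers no second look at the filtered result.

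The second strand is one of wording against design. A reader of the abstract, the Objectives or the Discussion would expect a non-inferiority conclusion on safety. No AE endpoint has a margin or decision rule from which to draw one.

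**Working it through.** **1. What the stated sample size covers.** Inputs from Sample size {14}: success 91% in both arms, margin 10 points, one-sided 5%, power 80%, attrition 10%.

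- n per arm = (1.645 + 0.842)² × (0.91 × 0.09 + 0.91 × 0.09) / 0.10² = 6.18 × 0.1638 / 0.01 ≈ 101.3, rounded up to 102.
- With attrition: 102 / 0.9 = 113.3, rounded up to 114 per arm, 228 in total.

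This reproduces the plan's figure exactly, so the sizing is not in dispute. It also shows that the sizing rests wholly on absence of the composite endpoint. The article gives no AE rate and no AE margin, so a non-inferiority test on AEs could not be sized from it.

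**2. Which events pass through the relatedness filter.**

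| Event | Where | Relatedness required? |
|---|---|---|
| Deep incisional or organ/space infection | Primary endpoint | No |
| CSF leakage, intraoperative or percutaneous | Primary endpoint | No |
| Pseudomeningocele needing intervention, or above 20 cc | Primary endpoint | No |
| Complications needing surgical re-intervention | Secondary endpoints | No |
| Other SAEs | Secondary endpoints | Unclear: the adjective may or may not govern them |
| Other AEs, such as delayed wound healing without reoperation | Secondary endpoints | Yes |

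**3. How differential labelling acts.** Let p be the all-cause AE rate, equal in both arms, and let s₁ and s₀ be the probabilities that an AE is labelled device-related in the LIQOSEAL and control arms. The filtered endpoint then shows a difference of p × (s₁ − s₀). None of these values is in the article; all are assumptions.

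| p | s₁ = 0.5, s₀ = 0.5 | s₁ = 0.6, s₀ = 0.4 | s₁ = 0.8, s₀ = 0.4 |
|---|---|---|---|
| 10% | 0 points | 2 points | 4 points |
| 20% | 0 points | 4 points | 8 points |
| 30% | 0 points | 6 points | 12 points |

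Swapping s₁ and s₀ reverses the sign. The filter can also conceal: if one arm truly has 12% and the other 24%, labelled at one half and one quarter, both show 0.12 × 0.5 = 0.24 × 0.25 = 6%, and a true doubling vanishes. In every row the all-cause comparison is unaffected by the label.

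**The case against.** The strongest reply is that safety does not hang on this one endpoint. Re-intervention complications are counted whatever their cause. The primary composite includes deep or organ/space infection, together with CSF leakage and pseudomeningocele, again without attribution. A reader might infer that the whole safety assessment is limited to device-related events, or that the trial's formal safety conclusion rests on this label. The documents do not support either inference: much of what matters most after this surgery lies outside the filter, and no success rule is attached to the AE endpoint. That part of the reply stands.

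A reader might also infer that unblinded investigators assign the label. The article says that they report events, not who judges relatedness. The full protocol is unpublished and the DMC charter is not shown; either could provide for adjudication. Nor is it established that SAEs are filtered, since the sentence can equally mean device-related AEs plus all SAEs. These limits stand too.

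It can further be said that all AEs are recorded, that {20c} sets AE denominators without mentioning relatedness, and that tabulation is normal analysis-plan content. This is true, and nothing bars an all-cause table. But the article does fix the definition of the endpoint, and it fixes it on the filtered events. That is a stated choice, not a detail left for elsewhere. The invented rates in the illustration show only how the mechanism works; they are not evidence that bias will occur.

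**Conclusion.** The point holds for one of the two secondary safety endpoints, and for AEs in particular. Its definition depends on a causal judgement in a trial where the surgeon and those assessing patients after surgery know the device, and no sensitivity analysis for safety is planned. Whether SAEs are affected depends on how an ambiguous sentence is read. The size and direction of any bias cannot be determined from the documents; the 2 to 12 points above rest entirely on assumed rates and labelling probabilities.

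The mismatch over non-inferiority is independent of who judges relatedness. The abstract, Objectives and Discussion extend the claim to safety, whereas the margin, sizing and test apply only to the composite, which speaks to safety only through its own components, such as wound infection.

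**What to change.** - Define the main AE comparison as all AEs and all SAEs up to 90 days, by randomised arm and regardless of attribution, reported as estimated differences with confidence intervals. This also removes the ambiguity over SAEs.
- Keep device-related events as a further tabulation, and state who assigns relatedness.
- Reword the abstract's Discussion paragraph, Objectives {7} and the main Discussion so that non-inferiority refers to the composite primary endpoint only, and AE safety is described as an estimated comparison.

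No new data are needed, because all AEs already go into the e-CRF. The cost is not nil. The trial was recruiting when the article appeared, so changing a secondary endpoint calls for an amendment, with the agreement and notifications described in section {25}. All-cause tables will also contain background surgical events and so be noisier.
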